### Remission

According to the Remission in Schizophrenia Working Group, remission for patients with schizophrenia is defined as a mild score (= 3 or lower) over a six-month period on all eight items of PANSS considered representative of the core symptoms of psychosis: delusions, hallucinations, positive formal thought disorder, bizarre behavior, affective flattening, avolition-apathy, anhedonia-asociality, alogia; or a mild score (= 3 or lower) over a six-month period on all seven items of BPRS considered representative of the core symptoms of psychosis: grandiosity, suspiciousness, unusual thought content, hallucinatory behavior, conceptual disorganization, mannerism/posturing, blunted affect [52,53].

### Relapse

For the purpose of this study, relapse is defined as any score equal to five or higher - for one month out of two or more - on the core symptoms of psychosis on the BPRS or PANSS, as defined above.

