The CGI is a tripartite rating scale aimed at assessing the severity of the patient at the moment of the assessment, improvement or worsening relative to the baseline, and efficacy of treatment (described in [34]). The CGI-severity rating is provided on a seven-point scale that assesses severity of the patient on the basis of total clinical impression: 1) not at all ill; 2) borderline mentally ill; 3) mildly ill; 4) moderately ill; 5) markedly ill; 6) severely ill; or 7) extremely ill. The CGI-change is provided on a seven-point scale, rated as: 1) very much improved; 2) much improved; 3) minimally improved; 4) no change; 5) minimally worse; 6) much worse; or 7) very much worse. The CGI-efficacy index is a rating scale crossing the efficacy of the treatment by occurrence of side effects: 1) unchanged to worse; 2) minimal efficacy; 3) moderate efficacy; 4) marked efficacy, with side effects rated as: 1) none; 2) does not interfere with patient’s functioning; 3) interferes with patient’s functioning; 4) outweighs therapeutic effects. A higher score on the CGI-severity and the CGI-change rating corresponds to greater severity and worsening, respectively. Conversely, a higher score on the CGI-efficacy index corresponds to better efficacy (however, greater side effects counterbalance efficacy).

The BPRS is a 24-item measure of general psychopathology in a Likert format, with scores from 1 (absent) to 7 (extremely severe) [35,36]. Possible BPRS total scores varied from 24 to 168. The primary purpose of the BPRS is to allow assessment of treatment change across a comprehensive set of common symptom characteristics. The original 16-item BPRS was initially expanded to 18 items, then to 24 items by adding 6 symptom items (bizarre behavior, self-neglect, suicidality, elevated mood, distractibility, and motor hyperactivity) to increase sensitivity to a broader range of psychotic and affective symptoms [37]. A higher score on the BPRS corresponds to greater psychopathology.

The PANSS is a measure of the current symptoms of patients on a 30-item scale [38,39]. The PANSS consists of three domains: positive symptoms, negative symptoms, and general psychopathology. Items are rated from 1 (absent) to 7 (extremely severe); the total score varies from 30 to 210. A higher score on the PANSS corresponds to greater psychopathology.

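### Relapse and remission can each be met on either BPRS or PANSS, but the two core-symptom lists differ, so one patient can meet both definitions and persistent negative symptoms alone can count as relapse

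*Protocol article*

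**What the plan says.** All references are to the protocol article.

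- **Remission.** There are two routes. The first is "a mild score (= 3 or lower) over a six-month period on all eight items of PANSS", listed as "delusions, hallucinations, positive formal thought disorder, bizarre behavior, affective flattening, avolition-apathy, anhedonia-asociality, alogia". The second is "or a mild score (= 3 or lower) over a six-month period on all seven items of BPRS", listed as "grandiosity, suspiciousness, unusual thought content, hallucinatory behavior, conceptual disorganization, mannerism/posturing, blunted affect".
- **Relapse.** The section states that "relapse is defined as any score equal to five or higher - for one month out of two or more" and that this applies "on the core symptoms of psychosis on the BPRS or PANSS, as defined above". The item lists are therefore those of the Remission section.
- **Assessment and outcome measures, Table 3.** BPRS and PANSS are both rated at T0, T1, T2 and T3.
- **Role of relapse.** The abstract makes changes in relapse and readmission the secondary objectives. Data management and analysis uses the first relapse or readmission as a terminal event for Kaplan-Meier and log-rank analysis.
- **Role of remission.** It is defined, but it is in neither the list of secondary outcomes nor the planned analyses.

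**The concern.** Within one scale and one list, the two states cannot coexist: remission needs every item at 3 or lower, and relapse needs some item at 5 or higher. Joining two lists with an either-or in both definitions breaks this exclusion wherever the lists differ. Nothing in the article says which scale prevails, that relapse cancels remission, or that relapse must be a worsening from a better state.

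The stake is the relapse endpoint. The Discussion paragraph of the abstract ties adoption of the programme in the national health system partly to fewer relapses. If lasting negative symptoms or rating error can produce the event in patients who have not worsened, such events should occur about equally in both arms and pull the comparison towards no difference.

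**Working it through.** **1. The lists side by side** (from the Remission section; the matching of similar names is mine)

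| Symptom | PANSS list | BPRS list |
|---|---|---|
| Hallucinations | yes | yes |
| Delusions / unusual thought content | yes | yes |
| Thought disorder / conceptual disorganization | yes | yes |
| Bizarre behavior / mannerism, posturing | yes | yes |
| Affective flattening / blunted affect | yes | yes |
| Avolition-apathy, anhedonia-asociality, alogia | yes | no |
| Grandiosity, suspiciousness | not named | yes |

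That gives 8 + 7 = 15 item ratings on about 5 + 3 + 2 = 10 distinct symptoms. Grandiosity and suspiciousness may be partly caught under PANSS delusions, so the three negative items are the firmer mismatch.

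**2. The definitions applied to one patient.** All seven BPRS items stay at 3 or lower for six months, and PANSS alogia stays at 5. Remission is met through BPRS and relapse through PANSS over the same period. The reverse case is all eight PANSS items at 3 or lower with BPRS grandiosity at 5. This step needs no assumption.

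**3. Size of the effect on relapse.** The plan gives no relapse rate, event count or power to reproduce; its sample size rests on adherence only. What follows is a simulation on assumed inputs: 200,000 patients whose true state never changes, four visits, between-patient SD 1.0, within-domain correlation 0.5, rating error independent by scale and visit, and scores rounded to 1 to 7. PANSS delusions is the maximum of three facets. A single rating of 5 or more counts as relapse, because visits six months apart cannot confirm a one-month duration. The table shows the share with a false relapse at t1 to t3 among patients with no score of 5 or more at t0.

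| Mean positive / negative item, error SD | Either scale | PANSS only | BPRS only | Either − PANSS | PANSS − BPRS |
|---|---|---|---|---|---|
| 2 / 2.5, 0.4 | 0.145 | 0.117 | 0.056 | 0.028 | 0.061 |
| 2 / 2.5, 0.6 | 0.277 | 0.218 | 0.120 | 0.059 | 0.098 |
| 2 / 3, 0.4 | 0.221 | 0.188 | 0.074 | 0.033 | 0.114 |
| 2 / 3, 0.6 | 0.378 | 0.317 | 0.149 | 0.061 | 0.168 |
| 2.5 / 3, 0.4 | 0.276 | 0.225 | 0.118 | 0.051 | 0.107 |
| 2.5 / 3, 0.6 | 0.453 | 0.370 | 0.217 | 0.083 | 0.153 |

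The either-scale rule itself adds about 3 to 8 points over PANSS alone. With rating error shared between the scales, this becomes about 2 to 6 points.

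Of the whole excess over BPRS alone, PANSS alone already accounts for 62% (0.098/0.157) to 78% (0.114/0.147). Without its three unmatched negative items, the PANSS list covers symptoms that are also on the BPRS list, so those three items drive this part.

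Of patients in BPRS remission over t0 to t1, 4% to 14% have a PANSS core item at 5 or more at t1.

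**4. Effect on power (illustration).** Assume true relapse of 40% versus 25% and 340/2 × 0.8 = 136 patients per arm. A false-relapse share f in both arms turns these rates into 0.40 + 0.60f and 0.25 + 0.75f, so the difference becomes 0.15 × (1 − f).

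- f = 0: 0.400 versus 0.250, power 75.5%
- f = 7.7%: 0.446 versus 0.308, power 65.5%
- f = 14.0%: 0.484 versus 0.355, power 57.8%

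This assumes that the wider rule catches no extra true relapses. In runs that modelled true relapses in positive symptoms, the either-scale rule had about the same power as PANSS alone, and the seven BPRS items had roughly 3 to 16 points more than the either-scale rule.

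**The case against.** The strongest case is that this is a wording gap with little consequence.

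- **Remission is not analysed.** This stands. No planned comparison uses both states, so a reader who infers that relapse rates become uninterpretable beside remission goes beyond the article.
- **The noise is mostly not due to the either-or.** This stands. It is tempting to attribute the whole 15% to 45% in the either-scale column to the union, but PANSS alone gives 12% to 37%.
- **Fifteen ratings are not fifteen independent chances of error.** This stands. They cover about ten symptoms, and Recruitment and baseline procedures gives each unit one assessor, so errors are probably shared.
- **The duration requirement is ignored.** This stands in part. A patient rated 4 on one scale and 5 on the other at one interview does not meet the relapse definition as written, because no duration is shown. If the same item had to reach 5 on two independent ratings, at an assumed 1% error per item, the false-relapse chance over 15 ratings would fall from 14.0% to 0.15%. But Table 3 schedules no ratings that could show this. A true, lasting negative symptom would pass a duration test anyway.
- **A scale hierarchy belongs in the full protocol or analysis plan.** This does not stand. The article does not leave the rule open; it states one, and that rule allows the contradiction.
- **Choosing BPRS is a preference.** This stands in part. The remark that "The primary purpose of the BPRS is to allow assessment of treatment change across a comprehensive set of common symptom characteristics" is a general description, not a reason to exclude PANSS. One PANSS list would also make the states exclusive.

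**Conclusion.** The point holds as an inconsistency between two definitions. That a patient can meet both over overlapping windows follows from the text alone. The two states are defined over periods, so the article does not support the stronger statement that a single visit's scores establish both.

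The practical harm is limited to the relapse endpoint, which is over-inclusive and somewhat diluted. Its size cannot be derived from the documents. The 2 to 8 points added over PANSS alone, and the larger gap to BPRS alone, rest on assumed item means, spread, correlation and rating error, and on counting single ratings. The power gain from the BPRS list further assumes that true relapses show in positive symptoms. The primary outcome and its sample size are unaffected. The change should be made, because relapse is a named secondary objective and a log-rank event, but the trial does not fail without it.

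**What to change.** Reconcile the Remission and Relapse sections by naming one scale and one item list for both definitions in the main analysis: remission when all listed items are 3 or lower, relapse when any listed item is 5 or higher, with durations still to be met. The states then exclude each other. Report the other scale's definition as a sensitivity analysis and drop the either-scale rule.

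The seven BPRS items are a reasonable choice, since only blunted affect among them is a negative symptom. The essential step is a single list, fixed before the data are unblinded.

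The cost is wording in two definitions; both scales are already collected at every visit. The downside is that worsening seen only on the other list counts only in the sensitivity analysis. With BPRS as the main scale, this means avolition, anhedonia or alogia, and the main relapse rate will be lower.

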### Readmission rate

Readmission is defined as any admission to a psychiatric unit to treat symptoms of psychosis or to change the drug regimen. Admissions for somatic reasons will not be considered as episodes of readmission. All voluntary and involuntary admissions of participants at enrollment during the study and at follow-up will be recorded.

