**Methods:**

340 patients diagnosed with schizophrenia and related disorders according to standardized criteria from 10 participating units distributed throughout the Italian National Health System (NHS), will be enrolled with 1:1 allocation by the method of blocks of randomized permutations. Patients will be reassessed at 6, 12 and 18 months after start of treatment (duration: 6 months).

The primary objective is to evaluate changes in adherence to pharmacotherapy after psychoeducation. Adherence will be assessed at three-month intervals by measuring blood levels of the primary prescribed drug using high pressure liquid chromatography, and via the Medication Adherence Questionnaire and a modified version of the Adherence Interview. Secondary objectives are changes in the frequency of relapse and readmission, as the main indicator of the course of the disorder.

Enrolled patients will be allocated to the FPP (yes/no) randomly, 1:1, in a procedure controlled by the coordinating unit; codes will be masked until the conclusion of the protocol (or the occurrence of a severe negative event). The raters will be blind to treatment allocation and will be tested for blinding after treatment completion. Intention-to-treat will be applied in considering the primary and secondary outcomes. Multiple imputations will be applied to integrate the missing data. The study started recruitment in February 2013; the total duration of the study is 27 months.

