### Aims

This study specifically set out to investigate the effectiveness of Falloon and co-workers’ Psychoeducation Program (FPP) and to evaluate its feasibility as part of the standard care setting provided by the INHS. The FPP will be compared to a control group, and randomized to a treatment with generic information on the disorders administered with the same frequencies as the FPP (Generic Treatment (GT)). We foresee that the FPP will be effective in improving adherence to pharmacotherapy in the exposed group when compared to the non-exposed group, and we also expect that the FPP will reduce the risk of relapse and readmission in the exposed group, by maintaining its effects at both six-and twelve-month follow-ups. Positive results would imply the importance of applying the FPP in all INHS settings, and the need of exploring its potential in other classes of psychosis, such as affective psychoses, which are also burdened by high personal, family and social costs.

A secondary goal of the study is the production of a manual to be used in the training and assessment of the professional staff involved in the treatment of patients diagnosed with schizophrenia-spectrum psychosis.

The primary outcome of the study, adherence to therapy, will be measured through a triple approach: a scaled self-report questionnaire, a four-query interview and, for the first time, the blood levels of the primary prescribed drug (to be measured by a specialized pharmacology unit with extensive experience in this type of studies). In this way, we will be able to validate the simpler instruments of measurement, such as the self-report or interview, with an objective, gold-standard method (blood levels of the therapeutic compound), a practice rarely used in past studies on adherence to therapy in patients with psychosis [27]. If one or both of the simpler, self-report instruments of assessment prove to be valid enough to differentiate adherent from non-adherent or partially adherent patients, the study will produce add-on information on easy-to-be-administered tools, to be generalized for future related studies.

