### Eligibility criteria

#### Inclusion criteria

Patients will be enrolled when they have a diagnosis of psychosis in the spectrum of schizophrenia according to the International Classification of Diseases - tenth edition (ICD-10: codes F20 to F29) and have been in contact with the unit for at least 24 months; admitting ages vary from 18 to 55 years old. Enrolled patients will be randomly allocated to FPP treatment (yes/no) with a rate 1:1, via a procedure controlled by the coordinating unit; codes will be masked until the conclusion of the protocol (or the occurrence of a severe negative event). Randomization will be carried out by the method of blocks of randomized permutations (to preserve balancing between the exposed and the non-exposed groups). Randomization will be stratified by location, due to the study’s multisite nature.

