### Assessment and outcome measures

Assessment is aimed at investigating the clinical and functional status of the patients and evaluating the main effects of treatment on the primary and secondary outcome measures (Table 3). The primary outcome is the patient’s adherence to pharmacotherapy, intended as the continuous use of the primary prescribed drug. Even if patients with psychosis are generally under poly-pharmacotherapy, only adherence to the most important drug (the one expected to produce the main therapeutic effect), as indicated by the enrolling unit, will be monitored during the study. Adherence will be checked by a triple method of assessment: patient’s self-report on the Medication Adherence Rating Scale (MARS), patient’s replies to the four-query interview of the Brief Adherence Rating Scale (BARS), and measurement of blood levels of the prescribed drug. Data will be analyzed using two indicators of adherence:

1. a dichotomic index, where non-adherence is the lack of adherence to the treatment in 30% or more of the monthly evaluation on the self-report or the interview (since replies on both measures might not coincide);

2. a continuous index based on the scale - self-report or interview - which could be the most reliable by comparison with the measurement of blood levels of the primary prescribed drug, to apply statistical analyses of covariance and verify the impact of confounding variables on the primary outcome.

**Table 3 T3:** Timing of assessments of endpoints for efficacy and safety

	**T0**	**T1**	**T2**	**T3**
Background information (age, sex, diagnosis, and so on)	X			
Clinical Global Impressions	X	X	X	X
Brief Psychiatric Rating Scale (BPRS)	X	X	X	X
Positive And Negative Syndrome Scale (PANSS)	X	X	X	X
Social Performance Scale	X	X	X	X
Health of the Nation Outcome Scales (HoNOS)	X	X	X	X
World Health Organization Quality Of Life (WHOQoL)	X	X	X	X
The Family Questionnaire	X	X	X	X
Medication Adherence Rating Scale	X	X	X	X
Brief Adherence Rating Scale	X	X	X	X
Dosage Record and Treatment Emergent Symptoms Scale (DOTES)	X	X	X	X
Sheenan-Suicidality Tracking Scale (S-STS)	X	X	X	X
Modified Overt Aggression Scale (MOAS) 1.0	X	X	X	X
Blood sample for assessing of the blood level of the prescribed drug	X	X	X	X
Assessment of blinding				X

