A number of related, secondary outcomes will be assessed: the occurrence of psychotic symptoms, according to the Brief Psychiatric Rating Scale (BPRS) and the Positive and Negative Syndrome Scale (PANSS); the general level of psychopathology, according to the Health of the Nation Outcome Scales (HoNOS); changes in social functioning, according to the Personal and Social Performance scale (PSP), and in the quality of life, as evaluated on the WHO-Quality of Life-Short form (WHOQOL-Bref); changes in the patient’s overall clinical status, as measured by the Clinical Global Impression (CGI); changes in the dosage of the prescribed drugs, as a reflection of changes in adherence to therapy; and, finally, changes in the frequency of relapse and readmission. Italian validated versions of the scales will be used. The BARS and the Family Questionnaire (see below) were translated for this study.

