### Data management and analysis

All analyses will be based, as far as possible, on the intention-to-treat principle. Differences in the primary outcome (adherence to pharmacotherapy) will be analyzed with a two-tail test for proportions with the Miettinen exact test [61]. A multiple logistic regression will be carried out to control for the confounding variables [62] using adherence (yes/no) as the outcome to verify the impact of the FPP on controlling the impact of the confounding variables (sex, age, severity of the disorder, cluster).

Survival analyses will be performed using the Kaplan-Meier method, followed by the log-rank test to define the terminal events at both the start of non-adherence and the first relapse or readmission episode [63]. Intention-to-treat will be applied considering the primary and secondary outcomes [64]. Multiple imputations will be applied to integrate missing data [65].

As far as validation of the self-report (MARS) and the interview (BARS) measure of adherence with respect to the blood levels of the main prescribed drug is concerned, Spearman’s rho will be used to compare blood levels of the main drug with the self-report or the interview; partial correlation will be used to ascertain the links between blood levels of the main drug with the self-report or the interview by taking into account the other measures (the interview or the self-report, respectively).

All analyses will be done with Excel (Microsoft Excel 2013 running on Windows 8) (Chicago, IL 60606, USA) or the Statistical Package for Social Science (SPSS) version 17 for Windows.

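### Readmission is worded as a change in frequency, but no pre-enrolment reference period is stated and the only stated analysis is an unadjusted time to first event

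*Protocol article*

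**What the plan says.** The abstract (Methods) states: "Secondary objectives are changes in the frequency of relapse and readmission, as the main indicator of the course of the disorder". The list of secondary outcomes under Assessment and outcome measures ends the same way: "and, finally, changes in the frequency of relapse and readmission".

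The section Readmission rate defines the event and then gives the recording window: "All voluntary and involuntary admissions of participants at enrollment during the study and at follow-up will be recorded". It names no period before enrolment. Table 3 has no row for admissions. Its only entry that could hold history is "Background information (age, sex, diagnosis, and so on"), collected at T0.

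Under Data management and analysis, readmission is covered by Kaplan-Meier curves, "followed by the log-rank test to define the terminal events at both the start of non-adherence and the first relapse or readmission episode". The only covariates listed there, "sex, age, severity of the disorder, cluster", belong to the logistic model for adherence. No adjusted analysis of readmission is described.

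Two further statements matter. Aims puts the hypothesis as a comparison of arms: "we also expect that the FPP will reduce the risk of relapse and readmission in the exposed group". Inclusion criteria require that patients "have been in contact with the unit for at least 24 months".

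**The concern.** Three parts of the plan describe three different quantities. The objective is a change in a frequency. The data described are events from around enrolment onwards. The analysis is the time to a first event, which is neither a frequency nor a change. Most of the other secondary outcomes worded as changes are measured on scales with a T0 assessment in Table 3; readmission has no scheduled baseline.

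This matters in two ways. A report of change from before the trial would have no defined reference period, so it could not be set against an 18-month on-study rate. In addition, patients probably differ widely in their tendency to be admitted, and past admissions probably predict future ones. If the prior count is not collected and used, that variation stays in the error and a chance imbalance in it cannot be adjusted for directly. An analysis plan written later can add a covariate to a model, but it cannot supply a count that nobody recorded.

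**Working it through.** **1. Is there a stated figure to reproduce?** Not for readmission. The sample-size section concerns adherence alone, and its figures reproduce:
- n per arm = 2 × ((1.960 + 0.842) / 0.45)² = 77.5, so 78.
- Design effect = 1 + (16 − 1) × 0.05 = 1.75, and 156 × 1.75 = 273.

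None of these figures changes with the present point. I use 273 / 2, about 136 per arm, only as a convenient size for the illustration in step 3.

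**2. Objective, data and analysis side by side.**

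| Element | Where | Quantity | Needs a pre-trial count? |
|---|---|---|---|
| Objective and outcome list | Abstract; Assessment and outcome measures | Change in frequency | Yes, if change is from before the trial |
| Hypothesis | Aims | Lower risk in the FPP arm | No |
| Recording window | Readmission rate | Admissions at enrolment, on study, at follow-up | No look-back named |
| Analysis | Data management and analysis | Time to first relapse or readmission, log-rank | No |

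Hypothesis and analysis agree with each other and are valid by randomisation. The wording of the objective is what the described data and analysis do not match. A change between on-study periods (treatment, first and second follow-up) can still be computed; a change from before the trial has no stated reference.

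**3. What would a prior count be worth?** The documents give no correlation r between prior and on-study counts, so r is an assumption. In a linear model, relative to comparing follow-up counts alone (variance 1):
- adjusting for the prior count leaves variance 1 − r²;
- a raw change score has variance 2(1 − r);
- the sample-size equivalent of adjustment is 1 / (1 − r²) − 1.

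With 136 per arm, the effect detectable at 80% power without adjustment is 2.80 × √(2/136) = 0.34 SD. At that effect:

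| Assumed r | Variance, adjusted | Equivalent extra patients | Power, adjusted | Variance, change score | Power, change score |
|---|---|---|---|---|---|
| 0.3 | 0.91 | 9.9% | 84% | 1.4 | 66% |
| 0.4 | 0.84 | 19.0% | 86% | 1.2 | 73% |
| 0.5 | 0.75 | 33.3% | 90% | 1.0 | 80% |

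Adjustment helps throughout. The change score is worse than follow-up alone at r = 0.3 and 0.4, and only equal to it at r = 0.5.

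**4. Does a look-back fit the design?** The abstract gives 18 months from start of treatment to last assessment. An 18-month look-back has the same length and falls inside the 24 months of unit contact that eligibility requires.

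**The case against.** The strongest reply is that this article uses change loosely for a difference between arms. The sample-size section speaks of a change in non-adherence and quantifies it as 25.5% in one arm against 47% in the other. The primary objective is likewise worded as a change and tested by a two-group comparison of proportions. Read that way, the readmission hypothesis and the log-rank test are coherent and need no history. This largely stands: it shows that the randomised comparison is sound. It does not remove the mismatch, because a log-rank test on a first event does not estimate a frequency either.

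A reader might infer more than the text supports, in four ways:
- That no change at all can be computed. Change between on-study periods can.
- That admissions are recorded only from enrolment. The sentence is loosely punctuated; its reference to enrolment may cover an index admission or a history taken at entry, and the background row of Table 3 is an open list. Neither fixes a period, however.
- That the prior count is certainly in each unit's files. This is a plausible inference from the contact criterion, but it is not stated, and admissions elsewhere may be missing.
- That the missing history biases the comparison or leaves imbalance wholly uncorrectable. Randomisation is stratified by location, and prognostic scales such as CGI, BPRS and PANSS are taken at T0.

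It is also fair to say that covariate choice can be left to an analysis plan that is not shown, and that the 1 − r² gain does not carry over directly to a log-rank test. The first does not cover collection of the count; the second is why the figures above are an illustration only.

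**Conclusion.** The point holds as a mismatch of objective, data window and analysis for a secondary outcome, and as a missed opportunity for precision. Change from a pre-trial baseline is not supported by the text. The between-arm comparison is not biased, and no stated figure is wrong.

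The size rests on an assumed r of 0.3 to 0.5 and on a linear model: 9% to 25% less residual variance. The gain in a Cox or count model would differ and cannot be derived from the documents. This is a cheap improvement to a secondary outcome for which the article gives no power calculation, not a threat to the trial's main conclusion. If the full protocol already fixes a look-back period, what remains is to state it and give the count a role in the analysis.

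**What to change.** - At t0, record from unit records the number of psychiatric admissions in the 18 months before randomisation, using the article's own definition of readmission. Add it as a row in Table 3, and say whether an admission in progress at randomisation counts as history.
- Alongside the log-rank test, fit a site-stratified Cox model for first readmission, or a count model if frequency is the target, with the prior count as a baseline covariate.
- Report before/after change descriptively only, since a raw change score gains nothing over the range of r considered. Otherwise, reword the objective as a between-arm difference in readmission.

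The cost is one case-report-form field and a short record check for 340 patients. The article reports recruitment as already under way; because the history predates randomisation, it can be collected retrospectively for patients already enrolled, preferably by staff unaware of allocation. Admissions to other hospitals may be under-captured, but for the same reason this should not differ systematically between arms.
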